### Ethical Considerations

This study has been approved by the institutional review board (number 0000283) of ETR Associates and is registered on ClinicalTrials.gov (NCT04902820) [51].

## Results

This study was funded in 2019 with institutional review board approval in 2020. The PrEPTECH intervention was built over the next 1.5 years. Study recruitment was launched in February 2022 and completed in September 2022, with 229 participants recruited in total. Data collection was completed in April 2023, and analysis will be complete in September 2023. We expect to publish the results by the end of 2023.

## Discussion

### Overview

Despite the rapid expansion of telehealth services for PrEP in recent years, formal and rigorous evidence of their effectiveness is sparse. We describe the protocol for an RCT to assess the effectiveness, acceptability, and feasibility of a telehealth HIV PrEP care intervention, PrEPTECH, in increasing PrEP uptake among young cisgender men and transgender women who have sex with men. We hypothesize that participants in the intervention arm will show higher rates of PrEP uptake at both 3 and 6 months than those in the control arm and that PrEPTECH is a feasible and acceptable telehealth HIV PrEP care intervention for young cisgender men and transgender women who have sex with men.

### Limitations

One key limitation of this study is that it will rely on self-report data for PrEP uptake and adherence. In self-report, study participants may tend to overestimate their PrEP use. The use of electronic monitoring (such as medication event monitoring systems) and measurement of plasma or blood concentration yield more reliable measures of true PrEP use [52,53]; however, these were cost prohibitive for this study. Because we are using the same measurement approaches across both randomized groups, we do not anticipate differential bias across the study arms.

It is also worth noting that based on previous research from the PrEPTECH pilot study [36], in our original study proposal, we assumed 50% PrEP uptake in the control population and, therefore, calculated a sample size target of 400 participants, anticipating retaining 80% (n=320) of these participants at 180-day follow-up. However, 6 months into data collection, we revised our sample size calculations using the latest data on PrEP uptake in relevant populations and comparable research projects, including ongoing RCTs of digital interventions, to ensure that the participant sample size was adequate yet feasible given the resources required to enroll and retain participants.

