### Intervention

Participants allocated to the intervention arm of the study gained access to a web-based telehealth platform called PrEPTECH, which provides PrEP education via self-guided reading material, access to laboratory testing for PrEP eligibility delivered to a participant’s home, and optional SMS text messages or email reminders to aid in medication adherence. PrEPTECH also provides access to telehealth care and PrEP prescriptions for eligible patients asynchronously through a web-based form or synchronously through telephone appointments with the study clinician, an infectious disease physician with expertise in PrEP care licensed in California and Florida. The PrEPTECH intervention tested here is an extension of the piloted PrEPTECH intervention. A brief report on the results of the pilot also discusses the development of the initial intervention by a multidisciplinary team in concert with a previous CAB [42]. It was adjusted to serve a larger group and to be completely web-based. In the second version of PrEPTECH, we incorporated a home laboratory testing kit service, built a platform for offering web-based health evaluations, and developed back-end systems for PrEPTECH to enable the clinical team to review submitted information and communicate with participants. The site was also redesigned for mobile platform compatibility.

All participants who completed at-home laboratory testing and an asynchronous or telephone appointment with the study clinician for whom PrEP was indicated received a prescription for Truvada (emtricitabine, 200 mg or tenofovir disoproxil fumarate, 300 mg). Adult cisgender male participants aged 18 to 27 years received a free 30-day supply of PrEP and subsequently had to pay for PrEP medication through insurance, through patient assistance programs, or out of pocket, should they choose to continue taking PrEP. Adolescent cisgender male participants aged 15 to 17 years and adult transgender female participants aged 18 to 27 years received free PrEP medication for the duration of their 6-month participation in the study because these subgroups were not included in the pilot study of PrEPTECH. Knowing less about the suitability of this intervention for these susceptible populations, the study team opted to provide free medication to them for the duration of the study. PrEPTECH also provides support for signing up for PrEP access programs, prescription transfer, and coordination with community partners.

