### Participant Timeline

The entire 6-month web-based study is completed on the PrEPTECH website. A sequential illustration of participants’ experiences is shown in Figure 1.

Recruited prospective participants review web-based materials on the PrEPTECH website and elect whether to create a web account, which requires them to verify their email address and phone number and provide their name.After creating an account, prospective participants are screened for eligibility via a web-based survey. Those meeting the inclusion criteria proceed to step 3.Each participant then verifies their identity by providing a photo of themselves with a photo ID card or a link to a public social media profile that shows their name with a visible photo of themselves.Participants who provide identity verification are invited to complete the baseline web-based survey.Each participant is randomized after baseline completion, informed of their assignment, and provided with standardized web-based resources on PrEP access or brought to the first step of the PrEPTECH intervention.All participants are invited to take the midpoint survey 90 days after the baseline survey.All participants are invited to take the final survey 180 days after the baseline survey.

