### Outcomes

#### Primary Outcomes

PrEP initiation at 3 months after enrollment will be assessed using participant self-report of having taken at least one dose of PrEP medication between study enrollment and midpoint survey administration.

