##### PrEP Medication Prescription

PrEP medication prescription at 3 and 6 months after enrollment will be assessed through multiple measures, including self-report of having received a PrEP prescription at any point during the intervention, as well as documented medication prescription through study electronic health records (among eligible intervention arm participants only).

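### Using the same self-report question in both arms does not support the expectation of no differential bias, because participants know their arm and only one arm is supplied with PrEP

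*Protocol article*

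**What the plan says.** Under Primary Outcomes, PrEP initiation at 3 months is assessed by "participant self-report of having taken at least one dose of PrEP medication between study enrollment and midpoint survey administration". The Participant Timeline makes clear that the trial is unmasked: "Each participant is randomized after baseline completion, informed of their assignment".

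The arms differ in more than information. The Intervention section gives the PrEPTECH arm home test kits, contact with a study clinician, intake questionnaires that the clinician reviews, and "optional SMS text messages or email reminders to aid in medication adherence". Adult cisgender men in that arm "received a free 30-day supply of PrEP"; the other two subgroups get free medication for the six months of the study. The Control section describes a web page of public resources, with no access to PrEPTECH features. The Intervention section also states that no hair or blood-spot measure of drug exposure was collected.

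The Limitations section accepts that "study participants may tend to overestimate their PrEP use", and then argues: "Because we are using the same measurement approaches across both randomized groups, we do not anticipate differential bias across the study arms".

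Prescription data appear as a secondary outcome: self-report in both arms, and "documented medication prescription through study electronic health records (among eligible intervention arm participants only"). The Data Analysis section mentions written prescriptions only in the feasibility review, and says that a more detailed analysis plan will be agreed before the final analysis.

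**The concern.** The Limitations sentence treats equality of the measuring tool as if it were equality of the measurement error. That step needs a further condition: the chance that a non-user answers yes must be the same in both arms. The design gives no ground for assuming this. A participant who has been sent drug, reviewed by a clinician and reminded to take it may feel more pressure to report a dose than one who was shown a web page. Because the outcome needs only one dose, a single wrong yes moves a participant from failure to success.

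If over-reporting is larger in the intervention arm, the primary comparison is pushed towards a positive finding when there is no effect, and a real effect is exaggerated. This sentence is the article's only statement on whether self-report error differs by arm, so a reader would take more reassurance from it about the primary result than the design supports.

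**Working it through.** **Inputs from the protocol article (Sample Size).** Control uptake 20%, intervention uptake at least 40%, power 0.80, α = 0.05, 80 per arm after attrition and 96 enrolled. Sidedness is not stated; two-sided is assumed.

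**The plan's own figure.** With pooled variance under the null:

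n = [1.96·√(2·0.30·0.70) + 0.8416·√(0.20·0.80 + 0.40·0.60)]² / 0.20² = (1.270 + 0.532)² / 0.04 ≈ 81.2, so 82 per arm.

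The unpooled formula gives 79 and the arcsine formula about 80. The stated 80 is reproduced to within two participants, and 80/(160/192) = 96. The sample size is not in dispute.

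**Bias model (assumed, not in the documents).** Let p be true uptake and f the fraction of non-users who wrongly report a dose. Reported uptake is p + (1 − p)f. If true uptake is the same in both arms, the false difference is (1 − p)(f_int − f_con). It depends only on the excess in one arm, and it is zero only if the two fractions are equal.

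**Chance of a significant result with no true effect.** For reported rates a and b, n = 80 per arm and m = (a + b)/2:

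se0 = √[2m(1 − m)/n], se1 = √{[a(1 − a) + b(1 − b)]/n},

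probability = Φ[(|b − a| − 1.96·se0)/se1] + Φ[(−|b − a| − 1.96·se0)/se1].

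For f = 10% in the intervention arm only: b = 0.20 + 0.80·0.10 = 0.28, se0 = 0.0675, se1 = 0.0672. The first term is Φ[(0.08 − 0.1324)/0.0672] = 0.218 and the second 0.001, total 0.219.

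| f in intervention arm (control 0) | Reported uptake | Chance of significance |
|---|---|---|
| 0% | 20% v 20% | 0.05 |
| 5% | 24% v 20% | 0.09 |
| 10% | 28% v 20% | 0.22 |
| 15% | 32% v 20% | 0.41 |
| 25% | 40% v 20% | 0.79 |

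At 25% the reporting error alone produces the whole planned effect. At 30% true uptake, the 5%, 10% and 15% rows become 0.08, 0.15 and 0.28.

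**Relaxing the zero-control assumption.** With 5% over-reporting in control and 15% in the intervention arm, reported uptake is 24% v 32%, se0 = 0.0710, se1 = 0.0707, and the probability is 0.20. The same 10-point excess has much the same consequence.

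**Equal over-reporting with a true 20% v 40%.** If 10% of non-users in each arm over-report, reported uptake is 0.20 + 0.80·0.10 = 28% and 0.40 + 0.60·0.10 = 46%. The difference falls from 20 to 18 points, and power at 80 per arm falls from 0.79 to 0.66. If the 10% applies to the intervention arm only, the difference grows to 46% − 20% = 26 points.

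**What a tipping point would look like.** Suppose the trial reports exactly 40% v 20% at 80 per arm. Back-corrected intervention uptake is (0.40 − f)/(1 − f), with variance 0.40·0.60/[80(1 − f)²]; the control variance is 0.20·0.80/80. At f = 8% the corrected difference is 0.148 with standard error 0.0745, z = 1.98. At f = 9% it is 0.141 with standard error 0.0750, z = 1.88. Significance is lost between 8% and 9% excess over-reporting.

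All these figures are for an unadjusted comparison of proportions; the planned model is an adjusted logistic regression.

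**The case against.** The strongest reply is that the authors are candid. They call self-report a key limitation, they say better measures were too costly, and they write only that they do not anticipate differential bias. That is fair: a reader might infer that the article rules such bias out, or would present the result as free of it, and the text does not go that far. What stands is narrower: the reason offered for the expectation does not support it.

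Second, the direction and size are not established. No over-reporting rate is given, and setting control over-reporting to zero is the extreme one-sided case. Intervention participants may even report more carefully, knowing that kits, intake forms and prescriptions are tracked. This stands, and it is why the figures are shown as a range. It does not rescue the inference, which needs the error to be equal.

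Third, not every feature of the surveys differs by arm. The article describes survey payment without distinction by arm, and participants enter their own answers. A reader might count payment as a driver of differential error; the documents give no ground for that.

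Fourth, a missing check against prescription records could be left to the detailed analysis plan that the article defers. This also stands, so the absence of that check is not a finding in itself. Nor can the records settle the matter. PrEP can be obtained outside the study, a prescription is not a dose taken, and study records cover one arm only. Adding reported prescription to reported dose would only add a second self-report from the same unmasked participants. The restriction of the record-based measure to eligible participants concerns a single-arm secondary measure and has no bearing on the primary comparison.

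**Conclusion.** The point holds as a wrong inference in the text. In an unmasked trial with a one-dose self-reported primary outcome, and with drug, clinician contact and reminders in one arm only, a shared questionnaire gives no basis for expecting equal reporting error. Differential over-reporting is possible and could favour the intervention; the documents do not show that it occurred.

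The size depends on assumed rates. Excess over-reporting of 5% to 15% among intervention-arm non-users raises the false-positive chance from 5% to between about 9% and 41%, given 20% true uptake in both arms, 80 per arm, a two-sided 5% test and no over-reporting in control. Over-reporting that is equal in both arms works the other way and weakens a true effect. The logical point is firm; the magnitude is illustrative.

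**What to change.** Replace the Limitations sentence with a statement that, because participants know their assignment and the arms differ in contact and drug supply, differential over-reporting cannot be excluded.

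In the detailed analysis plan still to be agreed, add a tipping-point analysis of the primary outcome. Fix in advance a range of over-reporting fractions for each arm, re-estimate the treatment effect over that grid, and report the excess in the intervention arm at which significance is lost.

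As a descriptive check only, cross-tabulate reported initiation in the intervention arm against study prescription records, with all participants randomised to that arm as the denominator. State alongside it that outside sources of PrEP and prescriptions not taken mean that the discordant cells are not a false-report rate, and do not feed them into the tipping-point analysis as one.

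No new data are needed. The cost is a changed sentence and one extra analysis with a small table; the price may be a more cautious conclusion if the tipping point is low.

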### Conclusions

The study findings will be disseminated through open-access journals and academic conferences. A summary of the results will also be shared with all community partners, CAB members, and study participants and published via our agency’s website, newsletter, and social media channels. We anticipate that the study results will offer valuable evidence about the effectiveness, acceptability, and feasibility of telehealth HIV PrEP care interventions in this population.

## Appendix

Multimedia Appendix 1 Sample screenshots of the PrEPTECH intervention.

## Abbreviations

CAB: community advisory board
CONSORT: Consolidated Standards of Reporting Trials
LGBTQ+: lesbian, gay, bisexual, transgender, and queer
PrEP: pre-exposure prophylaxis
RCT: randomized controlled trial
STI: sexually transmitted infection
